#### Data analysis

At major time points and at study completion the findings will be reported according to the internationally recognised CONSORT statement for the reporting of cluster randomised control trials [54]. Data will be analysed on an intention to treat basis (ITT). Data will be analysed using STATA v10, and all analysis will take into account the clustering by GP practice. Survival curves would be calculated to estimate the cumulative incidence of diabetes. The difference in incidence of T2DM in the groups is tested using the two-sided log-rank test adjusted for cluster. Differences in secondary outcomes between the groups will be assessed using either linear for continuous outcomes or logistic for categorical outcomes regression with treatment group as the independent variable.

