### Phase 2: Cluster randomised trial

Phase 2 is designed to adhere to internationally recognised criteria for developing complex interventions and for undertaking and reporting cluster randomised controlled trials [33]. Randomisation will be conducted at the level of the GP practice by a researcher who is independent of the study team. Cluster designs are being used in other similar trials of lifestyle management interventions [34-36]. Practices will be randomised 1:1 to either the control arm or the intensive arm using stratification by list size (<6,000, ≥6,000), and ethnicity (% South Asian <21%, ≥21% (median level of % South Asian in the ADDITION-Leicester study [37]) with a block size of 4.

Participation in the study is summarised in Figure 1. A summary of the data collected at each time point is given in Table 1. The primary outcome data will be collected at 36 months. Additional data will be collected at 6, 12 and 24 months. The data collection will follow the same standard operating procedures as the baseline/screening data described in Phase 1. Additionally at the 3 year follow up a health resource one page questionnaire and the EQ-5D will be collected [38]. Records are kept on missed clinical visits; structured education programmes and telephone support as well as withdrawn subjects.

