#### Power calculation

Assuming a 3 year cumulative conversion rate to T2DM of 35% in the control group [44,45,50], an intra class correlation of 0.05 and a dropout rate of 20% (as seen in the Finnish Prevention Study [51]), we calculated that we would need 374 patients to consent per group to detect a 40% risk reduction in the intervention group – data from 44 practices, 17 participants per practice, with 80% power at the 5% significance level. For 17 participants to be recruited per practice we have assumed a participation rate of around 20%. For an average practice 500 people will be invited for screening, of these around 20% will have pre-diabetes (assuming a positive predictive value of 20% [24]). Therefore around 100 participants per practice will be eligible for the trial. Assuming a participation rate of 20% should give the 17 participants we need per practice. A participation rate of 20% has been seen in other studies in a similar population [19].

A 40% reduction in the relative risk of developing T2DM was chosen as a conservative interpretation of the current evidence. Several meta-analyses and a systematic review have shown that lifestyle intervention studies in those with IGT resulted in a ~50% reduction in the relative risk of developing T2DM [5,52,53]. An intention to treat analysis of 12-month follow-up data from a randomised controlled trial found that an intervention aimed at the promotion of physical activity, using methods that are similar to the proposed study, achieved a reduction in 2-hour glucose of 1.3 mmol/l compared to the control group [12]. A reduction of 2-hour glucose of this magnitude has been associated with around a 50% reduction in the relative risk of developing T2DM [52], which is consistent with the above evidence.

One secondary outcome will be the percentage of patients in each group with a 10-year CVD risk greater than 20% at end of 3 years. It is estimated that 55% of patients will have a CV risk greater than 20%. To detect a difference between the two groups of 20% points in the proportion of patients with a 10 year risk of >20% with 80% power and two alpha of 5% and an intra-practice correlation coefficient of 0.05 the required sample size is 180 in the two groups.

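### The primary log-rank test adjusts for cluster but not for the randomisation strata, and no between-arm estimate with a confidence interval is named; the cost is modest efficiency, not validity

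*Protocol article*

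**What the plan says.** Under Phase 2: Cluster randomised trial, the article states: "Practices will be randomised 1:1 to either the control arm or the intensive arm using stratification by list size (<6,000, ≥6,000), and ethnicity" (percentage South Asian, cut at 21%), "with a block size of 4". That makes four strata of practices.

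Under Data analysis, "all analysis will take into account the clustering by GP practice", and the primary test is stated thus: "The difference in incidence of T2DM in the groups is tested using the two-sided log-rank test adjusted for cluster". The descriptive output is also given: "Survival curves would be calculated to estimate the cumulative incidence of diabetes". Neither stratification factor nor any baseline covariate is named for the primary comparison. No hazard ratio, risk ratio or risk difference is named either, and no confidence interval between arms.

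Under Power calculation, the sample size is set "to detect a 40% risk reduction in the intervention group", from a 35% three-year conversion rate in controls, with an intra-class correlation of 0.05 and 20% dropout. Fasting and 2-hour glucose are measured in every participant (Baseline screening visit).

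**The concern.** One design feature, the clustering, is carried into the analysis; the other, the stratification, is not. Stratified randomisation balances the arms on the stratifiers. If those stratifiers predict the outcome, the true variance of the treatment comparison is smaller than the between-practice variance suggests. A test that ignores the strata still charges the full between-practice variance, so its standard error is too large, its true type I error falls below 5%, and it has less power than a test that uses the strata.

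The second part is what the reader of the result receives. A log-rank test yields a p-value. Survival curves give incidence by arm. Neither states how large the reduction is with its uncertainty, so the output as named does not show whether a 40% reduction is compatible with the data.

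Baseline glucose is a separate and weaker matter. It is not a stratification factor, so leaving it out gives up precision without distorting the p-value.

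**Working it through.** **1. The plan's own figure.** Inputs from Power calculation: 35% v 35% × 0.60 = 21%; two-sided 5%; 80% power; intra-class correlation 0.05; 17 per practice; 20% dropout.

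- Two proportions with pooled variance under the null: n = [1.96√(2 × 0.28 × 0.72) + 0.842√(0.35 × 0.65 + 0.21 × 0.79)]² / 0.14² = 160.3, so 161 per arm.
- Design effect 1 + 16 × 0.05 = 1.80; 161 × 1.80 = 289.8; 289.8 / 0.80 = 362.25.
- 362.25 / 17 = 21.3, rounded up to 22 practices per arm; 22 × 17 = 374.

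The stated 374 is reproduced once practices are rounded up. It takes no credit for strata or covariates.

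**2. Power without adjustment.** Completers per arm: 374 × 0.80 = 299.2, or 17 × 0.80 = 13.6 per practice. With the design effect on 17 (1.80), power is 0.814. On 13.6 completers, the design effect is 1 + 12.6 × 0.05 = 1.63 and power is 0.851.

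**3. Effect of ignoring the strata.** Let f be the share of between-practice variance that the strata explain. The document gives no value, so f is an assumption. With balanced strata:

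- True design effect: D = 1 + 12.6 × 0.05 × (1 − f). The unstratified test uses 1.63 whatever f is.
- True type I error of the unstratified test: 2[1 − Φ(1.96√(1.63/D))].
- Power: Φ[(0.14 − 1.96 × SE_test) / SE_true]. SE_true = √(0.3934 D / 299.2). SE_test = √(0.4032 × 1.63 / 299.2) = 0.0469 if unstratified, and √(0.4032 D / 299.2) if strata are used. Here 0.4032 = 2 × 0.28 × 0.72 and 0.3934 = 0.35 × 0.65 + 0.21 × 0.79.

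| f | D | Type I, unstratified | Power, unstratified | Power, strata used | Points forgone |
|---|---|---|---|---|---|
| 0% | 1.63 | 0.050 | 0.851 | 0.851 | 0 |
| 20% | 1.504 | 0.041 | 0.860 | 0.878 | 1.8 |
| 50% | 1.315 | 0.029 | 0.877 | 0.917 | 4.0 |
| 100% | 1.00 | 0.012 | 0.908 | 0.970 | 6.2 |

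Both power columns use the same true variance, so the comparison is like for like.

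**4. Simulation check.** The set-up was 44 practices in 4 strata, blocks of 4, 14 patients per practice, diabetes detected at three yearly visits, a cluster-robust log-rank test without and with strata, and 2,000 runs per scenario.

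- Strata not prognostic: type I error 0.054 v 0.061; power 0.89 v 0.90.
- Strata explaining about half of the practice variance: type I error 0.027 v 0.055; power 0.89 v 0.93.

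The direction and rough size agree with the table. The stratified test ran slightly above 5%. The Monte Carlo standard error is √(0.05 × 0.95 / 2000) = 0.005, so this is a small excess, but it argues for a small-sample correction with 44 clusters.

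**5. Why the effect measure should be named.** Under proportional hazards, a fall in risk from 35% to 21% is a hazard ratio of ln(0.79)/ln(0.65) = 0.547, not 0.60. The 40% target therefore reads differently on the two scales.

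**The case against.** The strongest reply has four parts.

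- *The premise is unproven.* The article does not say why these stratifiers were chosen, and nothing in it links list size to conversion. Percentage South Asian enters the risk score used for invitation (Phase 1), but participants must then have impaired glucose regulation, so what prognostic value remains among those enrolled is unknown. This stands: the size can only be given as a range that includes zero.
- *The plan meets its own target.* Power without adjustment is 0.814 to 0.851 against a planned 80%, and any error is on the conservative side. This also stands.
- *A condensed article may leave such detail to the full protocol or analysis plan.* This is true of covariate lists in general. Here, though, the article fixes the test, its sidedness and its single adjustment, and following that text gives an unstratified test.
- *Adjustment is not free of risk with 44 clusters.* The simulation gives this some support, and the fix allows for it.

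A reader might infer more than the document supports. One might say that p-values are certainly too large; that holds only if the strata are prognostic. One might set 85% power against 88% to 92% with adjustment (0.851 v 0.878 and 0.917), a gain of 2.7 to 6.6 points. That credits stratified randomisation to the adjusted test only, whereas it also raises the unadjusted test's power, to 0.860 and 0.877. One might add baseline glucose to the same argument, but its omission leaves the p-value valid, and the document gives no glucose-conversion relation from which to size a gain. One might also conclude that the economic evaluation lacks an effect to work with. Health economics takes 36-month diabetes incidence as an effect, and survival curves by arm supply it.

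**Conclusion.** The point holds as one of efficiency and reporting. The primary test as written does not reflect the stratified randomisation, and no between-arm estimate with an interval is named for a trial sized on a 40% reduction. If the strata explain 0%, 20% or 50% of between-practice variance, true type I error is 5.0%, 4.1% or 2.9% and the power forgone is 0, about 2 or about 4 points. These figures rest on the article's planning values, on balanced strata, and on an assumed share of variance explained. The test is valid and at worst conservative, and the planned power is met. The change is still worth making, because it uses only data that the trial already collects.

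**What to change.** Make the primary analysis a cluster-aware survival regression for incident type 2 diabetes. Discrete-time complementary log-log suits glucose tolerance tests done at 12, 24 and 36 months (Table 1); Cox is an alternative. Use practice frailty or cluster-robust standard errors, with a small-sample correction for 44 clusters. Include treatment, list-size stratum, percentage South Asian stratum, and baseline fasting and 2-hour glucose.

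Name the effect measure in advance: the hazard ratio or the 36-month risk ratio, with its 95% confidence interval. The risk ratio compares directly with the 40% target. Keep a log-rank test, stratified by the randomisation factors and adjusted for cluster, as a supporting analysis.

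The cost is a change of wording in the analysis section and the choice of a small-sample method. The strata are known at randomisation and both glucose values are measured at baseline, so no data collection or sample size changes.

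### Secondary outcomes are compared with treatment group as the only named independent variable, although baseline and repeated follow-up values are collected. A longitudinal model would use them at almost no cost.

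*Protocol article*

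**What the plan says.** The Data analysis section sets the secondary analysis in one sentence: "Differences in secondary outcomes between the groups will be assessed using either linear for continuous outcomes or logistic for categorical outcomes regression", completed as "regression with treatment group as the independent variable". The same paragraph states "Data will be analysed on an intention to treat basis (ITT") and "all analysis will take into account the clustering by GP practice". It names no baseline value, visit term or earlier measurement.

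The section on Phase 2 says the primary outcome data come at 36 months and "Additional data will be collected at 6, 12 and 24 months". Table 1 gives the schedule after baseline:

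- HbA1c, cardiovascular risk score, Metabolic Syndrome and seven-day step count: 6, 12, 24 and 36 months.
- OGTT (fasting and 2-hour glucose): 12, 24 and 36 months.

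The Power calculation assumes "an intra class correlation of 0.05 and a dropout rate of 20" per cent. It also sets one secondary outcome, the percentage with 10-year CVD risk above 20%, at the end of three years.

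Participants who develop diabetes during follow-up stay in the study. Under Baseline screening visit they have no further OGTTs; under the Phase 2 exclusion criteria they continue without the 120-minute sample. Either way, 2-hour glucose is no longer measured in them.

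**The concern.** The named model has no place for the baseline value or the intermediate visits. Fitted at 36 months, an ordinary linear or logistic regression uses only participants with a 36-month value, and the earlier measurements of everyone else play no part. Two things follow.

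- **Precision.** Baseline predicts the later value of most of these outcomes, and an arm-only model on raw values leaves that variance in the error term.
- **Bias.** The arm-only comparison is safe if loss is unrelated to outcome, and nearly so if it is related in the same way in both arms. The arms differ openly in contact: a booklet for controls, against six hours of education, three-monthly calls and yearly updates. Reasons for leaving could therefore differ by arm, although nothing in the document shows that they do.

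For 2-hour glucose the question does not depend on speculation about drop-out. The protocol itself stops the measurement after diagnosis, so missing values depend on the primary outcome, which the intervention is meant to change.

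**Working it through.** **1. Is the 20% loss already in the sample size?** Inputs from the Power calculation: 35% against 21% (a 40% relative reduction), ICC 0.05, 17 per practice, 20% dropout, 80% power, 5% two-sided.

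- Pooled two-proportion formula, per arm: [1.960 x sqrt(2 x 0.28 x 0.72) + 0.842 x sqrt(0.35 x 0.65 + 0.21 x 0.79)]^2 / 0.14^2, rounded up = 161.
- Design effect: 1 + 16 x 0.05 = 1.8, and 161 x 1.8 = 289.8.
- Dropout: 289.8 / 0.80 = 362.25, rounded up to 363.
- Whole practices: 363 / 17 = 21.4, rounded up to 22, and 22 x 17 = 374 per arm.

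The stated 374 is reproduced and includes the loss. Power with 374 x 0.8 = 299 analysed per arm is 81.4%.

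**2. How many participants have only earlier values?** 374 x 0.20 = 74.8, about 75 per arm or 150 of 748. This counts everyone lost by 36 months. Those lost before any follow-up visit have a baseline value only.

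**3. Possible bias.** The document gives no SD, visit correlation or drop-out mechanism, so this is illustrative. Assumptions: 44 practices x 17, SD 1, ICC 0.05 (the diabetes figure, borrowed), visit correlation parameter 0.6 to 0.8, about 20% loss, true 36-month effect -0.20 SD. The ranges cover several sets of simulated trials with slightly different correlation patterns. In the one-arm scenario the log-odds of leaving rises by about 0.7 to 0.8 per SD of worse last value in the intensive arm and is unrelated to outcome in controls.

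| Loss mechanism | Arm only, raw 36-month value | Arm only, change from baseline | Baseline-adjusted | Longitudinal |
|---|---|---|---|---|
| At random, or alike in both arms | -0.19 to -0.20 | about -0.20 | about -0.20 | about -0.20 |
| Intensive arm only | -0.25 to -0.33 | -0.16 to -0.19 | -0.23 to -0.24 | -0.19 to -0.21 |
| Opposite directions by arm (0.7) | -0.34 | not run | not run | -0.20 |

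In the one-arm scenario, raw values overstate the effect by 0.05/0.20 = 25% to 0.13/0.20 = 65%. Change scores understate it by 0.01/0.20 = 5% to 0.04/0.20 = 20%. With the mechanism halved to 0.4, raw values give -0.22 to -0.245 and change scores -0.18 to -0.19.

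**4. Precision.** If r is the correlation between baseline and the 36-month value, using baseline multiplies the SE of the raw-value comparison by about sqrt(1 - r^2). That is 0.80 at r = 0.6 and 0.60 at r = 0.8, up to about 40% smaller. If correlation decays strongly over the visits, r is lower and the gain is small. Beyond baseline adjustment, the longitudinal model's SE is only 1 to 4% smaller. The gain also requires baseline to be tied across arms: when each arm kept its own baseline mean, the SE was about 0.10 with or without the earlier values.

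**5. Two-hour glucose.** Assumptions: SD 1.8 mmol/l, correlation 0.6, conversion 33% against 21% (close to the plan's 35% and 21%), no other loss. About 25% of controls and 15% of the intensive arm then have no 36-month value, and a true difference of -0.60 mmol/l appears as about -0.43 among those measured. The understatement is 0.17/0.60 = 28%.

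**The case against.** The strongest objection is that the article is a condensed account. Visit structure and missing-data handling commonly sit in a full protocol or SAP, and their absence here is no finding. That stands. The point concerns only the model that the article does state and the single term that it names.

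A reader might infer three stronger claims that the document does not support.

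- **That outcomes are analysed one visit at a time on attenders, contradicting intention to treat.** The text says neither. A 36-month regression on those measured is the natural reading of a model without a visit term, but it remains an inference, and comparing arms at one horizon is a legitimate choice. Nor is treatment group the model's only element, because clustering must be taken into account.
- **That the effects will be overstated by about half.** This needs strong outcome-dependent loss in one arm only, and raw 36-month values. The Abstract speaks of changes and the Endpoints section of reductions. An arm-only regression on change scores fits the stated wording equally well and errs slightly the other way.
- **That the 20% loss undermines the trial's size or its main result.** It does not: 374 per group already allows for it, and the primary log-rank comparison is a separate analysis.

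It can also be said that a longitudinal model is partly a matter of preference. With benign loss the choice barely affects bias, and most of the precision gain comes from baseline alone. What remains is that the longitudinal estimate stayed close to the truth in every scenario tried, uses data already collected, and costs little.

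**Conclusion.** The point holds as an improvement to a stated analysis, not as an error that invalidates it. The named model leaves out baseline and intermediate values that the trial collects. Run at 36 months on raw values, it can have an SE well above what is achievable: the longitudinal SE is up to about 40% smaller if baseline and 36-month values correlate at 0.8, with much less gain if the correlation is weak. Bias is possible but not shown. It is near zero when loss is random or alike in both arms. Under one-arm loss it ranges from 25 to 65% overstatement for raw values to 5 to 20% understatement for change scores. These figures rest on assumed correlations and drop-out mechanisms that the document does not give.

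The firmest part is 2-hour glucose. Missingness there follows from the protocol's own rule and will differ by arm if the intervention works, so a plain comparison of those measured at 36 months should not be taken at face value. The primary outcome and the sample size are not affected.

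**What to change.** In Data analysis, replace the sentence on secondary outcomes as follows. If a SAP already specifies this, align the article's wording with it.

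- **Continuous outcomes (HbA1c, fasting and 2-hour glucose, Framingham risk, step count):** one longitudinal linear mixed model per outcome. Enter baseline as a response constrained equal across arms, or as a covariate. Include visit, arm-by-visit, an unstructured within-participant covariance and a random practice effect. Use all available values and report the 36-month arm contrast. Baseline as a response also keeps participants lost before their first follow-up visit. Glucose has three follow-up visits, the other outcomes four.
- **Metabolic Syndrome:** a corresponding repeated-measures logistic model with baseline status. State whether the odds ratio is conditional on practice and participant or marginal, because these are different quantities.
- **2-hour glucose:** the same continuous model, so that values up to diagnosis are used. State that missingness after diagnosis depends on the primary outcome, and that the simple 36-month comparison of those measured is not to be taken at face value.

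The cost is a revised sentence and a little more modelling; no new data or visits are needed. The downside is reliance on loss being explained by observed values. That is still an assumption, though a weaker one than a 36-month comparison of those measured requires.

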**Design:**

Cluster randomised controlled trial undertaken at the level of primary care practices. Follow-up will be conducted at 12, 24 and 36 months. The primary outcome is the incidence of type 2 diabetes. Secondary outcomes include changes in HbA1c, blood glucose levels, cardiovascular risk, the presence of the Metabolic Syndrome and the cost-effectiveness of the intervention.

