#### Endpoints and outcomes

The primary outcome aims to show the reduction in the incidence of T2DM at 36 months in people with screen-detected IGR. Secondary outcomes are reductions in HBA1c, blood glucose levels fasting and post glucose load, cardiovascular risk as calculated by the Framingham risk calculator [48] and the presence of Metabolic Syndrome as defined by NCEP ATP III [49], increasing seven day step count and cost-effectiveness of the intervention.

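### Clinical secondary outcomes are regressed with treatment group as the only named independent variable, although their baseline values and the stratification factors are available as covariates

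*Protocol article*

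**What the plan says.** The Data analysis section gives one sentence to the secondary outcomes: differences between groups are assessed by "either linear for continuous outcomes or logistic for categorical outcomes regression with treatment group as the independent variable". The only further condition is that "all analysis will take into account the clustering by GP practice". No other covariate is named.

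The Endpoints and outcomes section lists the outcomes concerned: "Secondary outcomes are reductions in HBA1c, blood glucose levels fasting and post glucose load, cardiovascular risk as calculated by the Framingham risk calculator", then Metabolic Syndrome, seven-day step count and cost-effectiveness. The Power calculation section adds the proportion with a 10-year CVD risk above 20% at three years. The abstract puts it as "Secondary outcomes include changes in HbA1c, blood glucose levels, cardiovascular risk, the presence of the Metabolic Syndrome", which may or may not mean change scores.

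Table 1 schedules HbA1c, the OGTT, the cardiovascular risk score, Metabolic Syndrome and step count at baseline. On allocation, the Phase 2 section says "Practices will be randomised 1:1 to either the control arm or the intensive arm using stratification by list size" and by percentage South Asian, in blocks of 4.

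**The concern.** The sentence fixes a model and names its independent variable. Allowing for clustering makes the standard error honest, but it neither recovers the precision held in the baseline value nor corrects a chance difference between arms at baseline.

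Only 44 practices are randomised, 22 per arm. With any within-practice correlation, chance baseline differences are larger than in an individually randomised trial of the same size. If final values are regressed, such a difference passes into the estimate in proportion to the correlation between baseline and follow-up. If change scores are regressed, it is over-corrected. The binary outcomes (Metabolic Syndrome, CVD risk above 20%) get no help from the change-score reading.

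At stake are the width of the secondary confidence intervals and how far the estimates depend on chance imbalance. Because the article leaves final values and change scores both open, there is also an unfixed choice of estimate.

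**Working it through.** **The plan's own figure.** Inputs from Power calculation: 35% control rate, 40% relative reduction (so 21%), ICC 0.05, 20% dropout, and "data from 44 practices, 17 participants per practice, with 80% power at the 5% significance level". The two-proportion formula, two-sided and without continuity correction, gives 161 per arm. Design effect: 1 + (17 − 1) × 0.05 = 1.8. Then 161 × 1.8 = 289.8, and 289.8 / 0.8 = 362.25, so 363. In whole practices, 363 / 17 = 21.4, so 22 practices, and 22 × 17 = 374. The stated 374 per group is reproduced and is not in dispute.

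**Assumptions.** The correlation ρ between baseline and 36 months is not in the document; I show 0.3 to 0.8, with 0.5 to 0.7 as the central range. The ICC of 0.05 is stated for T2DM incidence and for CVD risk above 20%, not for HbA1c, glucose or steps; applying it to these outcomes is also an assumption.

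**Unadjusted final values, continuous outcome.** After 20% dropout: 17 × 0.8 = 13.6 per practice, and 22 × 13.6 = 299 per arm. Design effect: 1 + 12.6 × 0.05 = 1.63. SE = √(2 × 1.63 / 299.2) = 0.104 SD. Detectable difference at 80% power: 2.80 × 0.104 = 0.292 SD.

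**Alternatives.** Relative to unadjusted final values, variance is 2(1 − ρ) for change scores and 1 − ρ² with the baseline value as covariate. Adjusted against change scores, the ratio is (1 − ρ²) / [2(1 − ρ)] = (1 + ρ)/2.

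| ρ | Change / final | Adjusted / final | Adjusted / change | Detectable difference, adjusted | Power at 0.292 SD, adjusted |
|---|---|---|---|---|---|
| 0.3 | 1.40 | 0.91 | 0.65 | 0.279 SD | 84% |
| 0.5 | 1.00 | 0.75 | 0.75 | 0.253 SD | 90% |
| 0.7 | 0.60 | 0.51 | 0.85 | 0.209 SD | 97.5% |
| 0.8 | 0.40 | 0.36 | 0.90 | 0.175 SD | 99.7% |

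A simulation (22 practices of 14 per arm, ICC 0.05, the same ρ between and within practices, 3,000 trials per setting) gave adjusted-to-final variance ratios of 0.91, 0.74 and 0.50 at ρ = 0.3, 0.5 and 0.7, in line with the formula.

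**Chance imbalance.** With 374 per arm and design effect 1.8, the SD of the baseline mean difference is √(2 × 1.8 / 374) = 0.098 SD, against √(2 / 374) = 0.073 SD under individual randomisation, a ratio of √1.8 = 1.34. The chance of an imbalance above 0.1 SD is about 31%, and above 0.2 SD about 4%. This ignores stratification, which would lower these figures for any outcome related to the strata.

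An imbalance of 0.1 SD moves a final-value estimate by 0.1ρ, that is 0.05 to 0.07 SD at ρ = 0.5 to 0.7, or about half to two thirds of the SE of 0.104. It moves a change-score estimate the other way by 0.1(1 − ρ), that is 0.05 to 0.03 SD.

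**The case against.** The strongest reply is that one condensed sentence names the comparison of interest and does not say that nothing else enters the model; covariates are often left to the analysis plan, which is not shown. Part of this stands. The text does not exclude adjustment, so a reader may not conclude that none will be made, and the lack of a repeated-measures structure is no finding. But the article goes further than silence: it names the independent variable. An analysis plan that adjusted for baseline would add to this text, and one that followed it literally would be inefficient.

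Several stronger readings are tempting and are not supported:

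- **That every secondary outcome has a baseline value.** Cost-effectiveness does not have a full one: "Additionally at the 3 year follow up a health resource one page questionnaire and the EQ-5D will be collected". It is also analysed separately, under Health economics.
- **That imbalance is simply uncorrected.** That is so for final values only; change scores over-correct it.
- **That the 25 to 51% gain applies throughout.** It is against final values, for continuous outcomes, under assumed correlations. Against change scores the gain is 25 to 15%. It does not carry over to the logistic models, where the odds ratio is non-collapsible.
- **That ethnicity and deprivation differences between practices go unchecked.** Stratification by percentage South Asian already limits the first, and the document gives no figures for between-practice differences in deprivation.
- **That a continuous Framingham analysis is missing.** Framingham risk is already a listed outcome, and linear regression is provided for continuous outcomes.
- **That the results would be biased.** Randomisation keeps the unadjusted estimate unbiased on average.

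**Conclusion.** The point holds as a free improvement to the secondary analyses. The model as worded uses neither the baseline value of any clinical secondary outcome nor the two stratification factors, and it does not say whether final values or change scores are analysed. Under either reading, baseline adjustment is at least as precise for continuous outcomes. At an assumed ρ of 0.5 to 0.7 its variance is 25 to 51% lower than for final values (equivalent to 1.33 to 1.96 times the participants) and 25 to 15% lower than for change scores (1.33 to 1.18 times). The detectable difference falls from 0.292 SD to between 0.253 and 0.209 SD, if the ICC of 0.05 applies to these outcomes. For Metabolic Syndrome and CVD risk above 20% the gain is mainly power and is not quantified here. The matter is one of precision and of imbalance in the realised allocation; it does not touch the primary log-rank test or the 374 per group.

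**What to change.** Replace the sentence on secondary outcomes with a statement that each clinical secondary outcome is analysed at follow-up by cluster-adjusted linear or logistic regression, with these terms:

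- treatment group;
- the baseline value of that outcome, or baseline status for Metabolic Syndrome and for CVD risk above 20%;
- the two stratification factors, list size and percentage South Asian.

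Using the follow-up value as the outcome with baseline as a covariate also settles the choice between final values and change scores. It should be fixed before outcome data are seen, since adjusted and unadjusted odds ratios are different quantities. Cost-effectiveness stays under its own section.

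The cost is wording only. The baseline values are already in the visit schedule, the strata are known for every practice, and no visit, sample size or primary analysis changes.
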